##### Quality of life

We will compare mean difference in quality of life score as measured by the post-fistula repair reintegration instrument [83] at 1–3 months compared to baseline using McNemar’s test by intervention and will separately model the trajectory of quality of life across our five assessment points using mixed-effects linear regression analysis of assessment points within individuals. Comparative effectiveness of the cup vs. cup + on quality of life will be assessed by comparing the respective quality of life change using paired t-test. Perceived leakage will be assessed similarly. As we observed a wide variability in baseline leakage in our feasibility study (63.2 ml ± 49.2) [84] and clinical cut points leakage reduction are not established, we will use quality of life estimates to identify a clinically significant leakage reduction. Quantitative measures of *short-term user acceptability* will be described using appropriate distributional statistics and compared between cup vs. cup + using paired t-test (continuous) or McNemar’s test (categorical). Quantitative measures of *long-term acceptability* will be described by cup vs. cup + through modeling their trajectory across community assessment and comparing these statistically using mixed-effects linear regression analysis. In secondary analyses we will assess various potential confounders will for association with the primary outcome variable (% change in volume of urine leaked at 6 h of use) as well as with user acceptability score. A direct relationship will also be assessed between effectiveness (self-perceived change in volume of urine leaked) recorded at 24 h of use and at 1, 2, and 3-month follow-up for both intervention models.

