**Methods:**

We describe a four-year clinical trial and nested qualitative study to examine the effectiveness and acceptability of an insertable vaginal cup to manage fistula urinary incontinence and understand fistula management costs. Two intervention models will be compared to a control: (1) vaginal cup (‘cup’), and (2) vaginal cup attached via tubing to a leg-secured urine collection bag (‘cup+’). Using a cross-over design, up to 100 participants will be block randomized to one of two sequences of leaking freely (no intervention), cup, and cup + at four fistula centers in Ghana and Kenya and observed for four days (400 total observations). Data will be captured through interviewer-administered survey, clinical exam and checklist. After clinic-based assessment, participants are individually randomized for cup or cup + for home use for up to 3 months and surveyed monthly. Effectiveness will be evaluated through quantitative comparison of urinary leakage (6 h and 24 h) and patient-reported quality of life (1–3 months) between cup, cup+, and leaking freely. Acceptability will be assessed quantitatively (1–3 months) and via in-depth interview among selected trial participants (*n* ~ 30) and potential implementers (*n* ~ 20).

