As acceptability, appropriateness, and other implementation barriers have been previously identified when implementing evidence-based tools for incontinence management, [48, 49] menstrual hygiene management, [31] and surgical management of fistula, [50, 51] contextualizing implementation while evaluating the impact of the cup and cup + is critical. Therefore, this study will evaluate the effectiveness and acceptability of a valved vaginal cup and a valved vaginal cup with tubing for non-surgical management of VVF, estimate fistula-related management costs, and understand the implementation context for the cups. Importantly, the comparison for effectiveness outcomes is not surgery but free leakage. Identification of effectiveness and acceptability for either intervention model could influence a shift in clinical fistula management practice paradigms. Qualitative findings from community assessment of the cup and cup + among users and fistula stakeholder interviews will help explain quantitative results regarding efficacy, effectiveness, or adherence.

We hypothesize that limits to the cup/cup + effectiveness for fistula incontinence management are likely to be attributable to acceptability and adherence [52]. While the use of cup/cup + for fistula incontinence management is novel, cups and other intra-vaginal devices for menstrual management, [53 contraception,^54^] and prevention of sexually transmitted infection [55, 56] are used when available and accessible and have been found to be acceptable throughout sub-Saharan Africa [57] To support a multi-dimensional understanding of both user and implementer acceptability and cost of cup/cup+, use of behavioral frameworks like the Theoretical Framework of Acceptability [58] can help identify how acceptability shapes user adherence and uptake and guide identification of optimal user and implementer characteristics. Our theory-oriented approach will inform generalizability of our effectiveness findings, provide an understanding of context, and help identify implementation strategies that may improve implementation outcomes, such as acceptability, appropriateness, and cost.

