##### Data collection

Data will be collected within the clinic-based phase via questionnaire, clinical exam (by a physician), clinical checklist (by nurse/midwife), pad test, and observation (Fig. 1; Table 2). At baseline, a gynecological exam will be carried out as potential participants are being screened and, once enrolled, the baseline questionnaire will be administered. Data will be directly entered into the REDCap mobile app to facilitate data privacy and quality. Next, all participants will be provided disposable pre-weighed adult pads or diapers for the first six hours of each treatment assignment while carrying out typical activities daily living activities on the ward. Six hours was deemed to be a clinically significant amount of time to provide women some relief from their leaking to allow them to engage in social activities or sleep uninterrupted. Additionally, six hours will likely provide those in the cup + assignment the opportunity to fill and then empty their leg bag. Lastly, six hours was deemed logistically feasible for data collectors (i.e., at the start and end of their shift). When assigned to cup or cup+, participants will also insert and wear the respective cups. Women will be encouraged to void ‘normally’ if they sense urgency and instructed to change their diapers as frequently as they see fit when they feel dampness and to deposit the used diapers into a personal plastic Ziplock bag that is then sealed until study staff can record the weight of the wet diapers. At the end of the first six hours of each treatment assignment, the weight of the participant’s assigned dry diapers will be subtracted from that of the wet diapers to calculate the volume of urine leaked, and participants will be asked questions regarding perceived effectiveness. Participants will continue with their assigned treatment until 24 h of use, at which time another questionnaire and a clinical checklist to note any adverse events will be administered by the study physician or nurse/midwife.

**Table 2 Tab2:** Quantitative study measurements, data sources, and timing of assessment

Category	Measure	Data Source^a^	Clinic				Community		
			0h	6h	24h	4d	1m	2m	3m
Outcome variables									
Quality of life ^b,c^	Quality of life (Post-fistula repair reintegration instrument)^*92*^	PS	●				●	●	●
Urine leaked (observed) ^c^	Pad weight; number of pads used, food and fluid intake, voiding	PT, TM		●					

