Urine leaked (perceived) ^c^	Perceived difference in leakage (cup, cup+, leak free)^90,91^	PS		●	●		●	●	●
Acceptability (patient, family, clinician) ^c^	Ease, comfort, interference, likelihood to use or recommend	PS		●			●	●	●
	Barriers to use, concerns, use decision-making process	PS				●			

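### Mean change from baseline in a 0–100 quality-of-life score is assigned to McNemar's test, which applies to paired binary data; the mixed model planned alongside it is suitable, so this is a should-fix correction

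*Protocol article*

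**What the plan says.** Only the protocol article is at hand. In Data analysis, under Quality of life, the quantity to be tested is a mean: "We will compare mean difference in quality of life score". The test named for it is McNemar's: "compared to baseline using McNemar’s test by intervention". The same sentence adds a separate mixed-effects linear regression, to "model the trajectory of quality of life across our five assessment points".

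Later in that paragraph, short-term acceptability is to be compared by "paired t-test (continuous) or McNemar’s test (categorical"). The sample size section on quality of life describes the instrument as standardised to 0–100, reports means and SDs for it, and sizes the cup versus cup+ comparison with a dependent t-test.

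In Table 2 (Data collection), the row "Quality of life (Post-fistula repair reintegration instrument") is marked at 0h and at 1, 2 and 3 months. The 6h, 24h and 4d columns are blank.

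The abstract's Methods paragraph presents the comparison as "patient-reported quality of life (1–3 months) between cup, cup+, and leaking freely". The Background says that "the comparison for effectiveness outcomes is not surgery but free leakage". Under Community-based procedures, women are individually randomised to take home the cup or the cup+, and nobody is assigned to leak freely at home.

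**The concern.** McNemar's test uses the discordant pairs of a paired two-by-two table. A mean difference on a 0–100 score gives no such table. To carry out the instruction, an analyst would first have to make the score binary, either at a threshold or as improved/not improved. The article defines neither, so the choice would be open after the data are seen, and either choice discards information.

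Quality of life matters here. It is one of the two outcomes named in the sample size section, and the analysis section says it will be used to identify a clinically significant reduction in leakage.

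Two smaller points sit beside this. The number of assessment points in the analysis text does not match the schedule. And the abstract's wording can be read as if leaking freely were a concurrent comparator during home use, when the only value without a device is each woman's own baseline.

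**Working it through.** **1. Test against scale.** The paragraph's own convention is paired t-test for continuous and McNemar for categorical measures. The score is 0–100 and summarised by mean and SD, so by that convention change from baseline calls for a paired t-test. The McNemar instruction contradicts it.

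**2. How the score was treated at design (background only).** The article gives N = 59 from a dependent t-test, two-sided alpha 0.05, power 0.85, difference 40%. Reading 40% as a standardised difference of 0.4, the normal approximation is n = ((1.960 + 1.036)/0.4)² = 56.1. The exact noncentral-t calculation gives n = 59 with power 0.856, which reproduces the stated figure. Read as 40 points with SD 28.1, the same test would need only 7. N = 59 was thus sized with a t-test on a continuous score. It concerns cup versus cup+, not change from baseline.

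**3. Cost of an improved/not-improved split.** Assumption: 40 women per arm, from 100 enrolled × 0.80 retained ÷ 2. The documents give only up to 100 women and more than 80% retention. Under normality, the asymptotic efficiency of the sign test relative to the paired t-test is 2/π = 0.637, and 40 × 0.637 ≈ 25.

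Power at n = 40, two-sided 0.05, uses the two changes quoted in the sample size section. The standardised change is d = mean/SD. The chance that a woman improves is Φ(d). The exact sign test rejects at 27 or more of 40 in one direction.

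| Change (SD) | d | Φ(d) | Paired t power | Sign-test power |
|---|---|---|---|---|
| 40.5 (28.1), all women in the cited cohort | 1.44 | 0.925 | about 1.00 | about 1.00 |
| 13.1 (28.9), those still leaking | 0.453 | 0.675 | 0.80 | 0.57 |

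The loss is immaterial at the larger change and appreciable at the smaller one.

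**4. Cost of a fixed threshold (simulation, all settings assumed).** Bivariate normal scores, baseline mean 36.7, SDs 19.0 and 22.7, SD of change 28.1. The implied correlation is (19.0² + 22.7² − 28.1²)/(2 × 19.0 × 22.7) = 0.10. The shift is 0.4 × 28.1 = 11.24 points. With n = 59 and 20,000 replicates, paired t power is about 0.86. McNemar after cutting the score at 30, 40, 50, 60 or 70 has power 0.35–0.67 (exact) or 0.45–0.75 (chi-square). The spread shows how far the result would depend on an unstated cut-point.

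**5. Number of assessment points.** Marked cells in the Table 2 quality-of-life row: 0h, 1m, 2m, 3m = 4, against five stated. The row that does carry five marks is "Perceived difference in leakage (cup, cup+, leak free"), at 6h, 24h, 1m, 2m and 3m. Whether that is the source of the five cannot be told from the article.

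**6. Comparator.** The home arms are cup and cup+. The value while leaking without a device is the 0h baseline. Each device's contrast with leaking freely is therefore a within-woman change over time, without a concurrent control and alongside education and monthly contact. Cup versus cup+ is the randomised comparison.

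**The case against.** The strongest reply is that a suitable analysis is already planned. The sentence that names McNemar also names a mixed-effects linear model of the same score, and that model can give the contrast of each month with baseline. This stands. A reader might infer that quality of life has no valid analysis; the article does not support that.

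Second, this is not the primary analysis. The primary outcome variable is percentage change in urine leaked at 6 h, the three primary comparisons concern six-hour leakage, and the quality-of-life contrast that was sized is cup versus cup+. This stands too and limits the severity.

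Third, a reader might infer that the plan in effect throws away 15 of 40 women per arm. The article states neither an arm size nor a dichotomy, and at the larger cited change nothing is lost. The figure holds only under the assumptions shown.

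Fourth, a reader might infer that the article claims a controlled home comparison with free leakage. The analysis section says compared with baseline, and Study design speaks of change in quality of life; both openly describe before-after change. Only the abstract and the general statement in the Background are loose. Regression to the mean is also thinly supported as an explanation, because entry requires leakage above 6 ml over 6 h and no quality-of-life threshold is stated. The effect of counselling and follow-up remains a fair caution.

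The reply does not rescue the McNemar instruction. The mixed model is described as separate and does not replace the test named for the baseline comparison.

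**Conclusion.** The named test is wrong for the named quantity and contradicts the paragraph's own convention. It should be corrected, but as a should-fix: the mixed model gives a valid route, and the outcome is not the primary one.

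The size of the harm is conditional. It arises only if the score is dichotomised so that McNemar can be run. With an assumed 40 women per arm and an improved/not-improved split, efficiency is about 0.64. The power lost then ranges from nil at a change of 40.5 (SD 28.1) to about 0.80 down to 0.57 at a change of 13.1 (SD 28.9). The article gives no expected change for the cup that would place it in this range.

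The mismatch of five against four assessment points is minor, since the mixed model uses whatever points are collected. The free-leakage point concerns wording, not the analysis itself.

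**What to change.** - In Data analysis, Quality of life, replace McNemar's test for change from baseline with a paired t-test within each home arm, or with the baseline-to-month contrast from the planned mixed-effects linear model, reported with a 95% CI. The second adds no new analysis. Keep McNemar for binary items.
- Reconcile the five assessment points with the four in the Table 2 quality-of-life row (0h, 1, 2 and 3 months).
- Reword the abstract, and qualify the general statement in the Background, so that home quality of life against leaking freely is described as an uncontrolled before-after change and only cup versus cup+ as a randomised comparison.

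The cost is wording only: no new data, visits or participants. The claim for quality of life against leaking freely becomes slightly more modest.

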**Fig. 2 Fig2:**
[figure not shown]
Participant flow diagram across clinic and community-based study components

This mixed-methods design allows for a more complete understanding of non-surgical management than quantitative or qualitative approaches alone, [62] emphasizing our primary outcome of effectiveness via robust assessment of clinical and patient-reported outcomes, and providing important acceptability and cost burden data to inform future implementation. Our approach maintains a focus on rapid translational gains for clinical intervention and useful information for key decision-makers.

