Cross-over trial designs provide greater efficiency than parallel designs due to within-subject treatment comparisons where each subject serves as their own control, resulting in lower sample size requirements for statistical power. Our sample size of up to 100 participants (400 observations) is calculated to assess: (1) a ≥ 65% reduction at six hours in observed urinary leakage, and (2) a mean 40% quality of life difference at three months between the cup and cup+ (measure range 0-100; Supplementary Figures). We expect > 80% retention over three months study follow-up based on our research with 12-months follow-up with 98% retention with this target population in Uganda^63^ and 3-months follow-up in Ghana with 84% retention, [64, 65] and have inflated our target sample size conservatively.

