#### Quality of life

Using dependent t-test with 2-tailed, alpha error = 0.05, estimated mean difference of effect between the cup and cup + of 40%, and power 0.85 to avoid type 1 error, required sample size is 59. Estimates of the effect are based on data collected within a longitudinal study of post-surgical fistula repair patients in Uganda, [66] wherein participants were asked about quality of life using the post-repair fistula reintegration measure which is standardized to a range of 0-100 [67]. Participants reported a mean of 36.7 (SD = 19.0) at the time of fistula repair (referring to living with fistula) and a mean of 78.0 (SD = 22.7) at follow up (6 months post-repair), reflecting a mean change of 40.5 (SD 28.1): 54.2 (SD 14.5) among those who were not leaking urine and 13.1 (SD 28.9) among those who continued leaking urine. The cup + is estimated to have a comparable improvement on quality of life as surgical repair, while the cup, based on our observations during our feasibility study [37] and on expert opinion, is estimated to have a smaller effect on quality of life over the long-term (3 months) as it has 1/15th of the capacity for urine storage and thus will need more frequent emptying than the cup+.

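### The cup vs cup+ quality-of-life comparison is sized at three months, but the window is given elsewhere as 1–3 months and the sentence naming the test gives no visit

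*Protocol article*

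**What the plan says.** **Sizing.** The Quantitative part of the sample size section lists two targets, the second being "a mean 40% quality of life difference at three months between the cup and cup"+. The Quality of life part of that section specifies one test: "Using dependent t-test with 2-tailed, alpha error = 0.05", an "estimated mean difference of effect between the cup and cup + of 40"%, power 0.85 and a required sample size of 59. It also ties the assumed device difference to the later time point: the cup "is estimated to have a smaller effect on quality of life over the long-term (3 months").

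**Window elsewhere.** The abstract's Methods evaluate "patient-reported quality of life (1–3 months) between cup, cup+, and leaking freely". The Study design section also puts the change in quality of life at one to three months. Table 2 schedules the instrument at baseline and at months 1, 2 and 3.

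**Analysis.** The Quality of life part of Effectiveness outcomes contains three statements:
- change from baseline at 1–3 months is assessed by intervention;
- the authors "will separately model the trajectory of quality of life across our five assessment points" with a mixed-effects linear model;
- for the two devices, "Comparative effectiveness of the cup vs. cup + on quality of life will be assessed by comparing the respective quality of life change" by paired t-test.

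The third statement names no visit.

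**The concern.** Quality of life is one of only two endpoints that set the sample size, and its requirement (59) exceeds that for leakage (50). The sizing fixes a visit. The sentence that specifies the device test does not, and it follows directly on a sentence whose window is 1–3 months. The change to be tested could therefore be read as month 3, as another visit, or as an average over the three.

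The choice can matter for three reasons:
- The device difference is argued as a long-term one, while the Background says acceptability may change over time. An early difference that fades and a lasting one are different answers.
- Home use is for up to three months, and women leave when surgery becomes available. Month 3 will be missing for some of them, so substituting an earlier visit or an average is a practical temptation.
- The same paragraph will use quality of life to decide what leakage reduction is clinically significant, and will analyse perceived leakage in a similar way.

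**Working it through.** **1. Reproduce the plan's figure.** Inputs from the sample size section: paired t-test, two-sided alpha 0.05, power 0.85, effect 40%. Reading 40% as a standardised paired effect dz = 0.40:
- Normal approximation: n = ((1.960 + 1.036)/0.40)² = 56.1, rounded up to 57.
- Noncentral t: n = 58.07, rounded up to **59** (power 0.850 at 58, 0.856 at 59).

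The stated 59 is reproduced. It corresponds to one test at 5%, on the contrast the section places at three months.

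**2. Set the texts side by side.**

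| Place | Device comparison on quality of life | Visit |
|---|---|---|
| Sample size, Quantitative | cup vs cup+ | three months |
| Sample size, Quality of life | cup vs cup+, t-test | three months (long-term effect) |
| Abstract, Methods | cup, cup+, leaking freely | 1–3 months |
| Study design | change in quality of life | one to three months |
| Analysis, first sentence | within each intervention, against baseline | 1–3 months |
| Analysis, device sentence | cup vs cup+, t-test of change | not stated |

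**3. What the open visit could cost under the null.** Assumptions, none of them in the article: four scores (baseline, months 1, 2, 3) with equal variance and a common correlation ρ, each contrast tested at two-sided 5%, and success claimed on any contrast in the set. Let V be the common factor (1 − ρ)σ².
- *Month-3 change and another visit's change.* Covariance V, variances 2V, so the correlation is 1/2 whatever ρ is. P(any of three visits significant) = **12.5%**.
- *Month-3 change and the average change over months 1–3.* Covariance (1 + 1/3)V, variances 2V and (4/3)V, so the correlation is (4/3)/√(2 × 4/3) = 0.816. P(either) = **7.7%**.
- *Month-3 change and the slope over all four scores*, weights (−1.5, −0.5, 0.5, 1.5). Covariance 3V, variances 2V and 5V, so the correlation is 3/√10 = 0.949. P(either) = **6.5%**.

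Simulated two-sample t-tests with 40 women per arm (80% of 100, assuming 1:1 allocation), with ρ from 0 to 0.9 and either exchangeable or autoregressive correlation, gave:

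| Contrasts allowed to count | False-positive risk |
|---|---|
| Month 3 only | 4.7–5.3% |
| Month 3 or slope | 5.9–6.6% |
| Month 3 or average | 7.1–7.9% |
| Any of three visits | 11.1–12.8% |

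Month 3 and the average gave different verdicts in about 4–5.5% of null trials.

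**4. An illustration under a fading effect.** Take the article's SD of change, 28.1, and 40 per arm: SE = 28.1 × √(2/40) = 6.28. A 15-point difference at month 1 (an assumed value) gives 15/6.28 = 2.39 and power of about 67%. If it has faded to zero by month 3, the chance of significance there is 5%. In that scenario the choice of visit settles the conclusion.

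**The case against.** The strongest reply is that a deciding contrast can be put together from what is written. One device test is named, a comparison of change, and the sizing places that comparison at three months. Within the analysis paragraph, the 1–3 month window belongs to the within-intervention sentence. The abstract line is a summary covering all comparisons. On that reading only a repeated phrase is missing.

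Most of this stands, and it rules out the stronger inference a reader might draw: that the plan has no deciding contrast and that its 5% error has become 10–16%. The documents do not support that, for four reasons:
- No rule lets any visit count as success.
- The trajectory model is not said to compare devices. For long-term acceptability the same paragraph does say so, which suggests the authors state a device contrast when they intend one.
- The named primary outcome variable is six-hour leakage, and the three primary comparisons are on leakage. The Study design phrase "emphasizing our primary outcome of effectiveness via robust assessment of clinical and patient-reported outcomes" is too general to make quality of life co-primary.
- Alpha allocation and testing order for a non-primary endpoint commonly belong in the analysis plan, which is not shown.

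What the reply does not remove is that the article gives two windows for quality of life and leaves the visit out of the one sentence that specifies the device test.

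**Conclusion.** The point holds as a mismatch between sizing and analysis. The device comparison on quality of life is sized at three months, described elsewhere over 1–3 months, and tested at a visit the analysis text does not name.

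Read with the sizing, the plan has one test at 5%. The inflated figures (about 6–8% if an average or slope joins month 3, about 12.5% if any of three visits may count) are scenarios, not properties of the written plan. They rest on an assumed visit correlation structure and, for the simulated ranges, on 40 women per arm. The point is worth correcting because quality of life drives the sample size and the correction is cheap.

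**What to change.** In the Quality of life part of Effectiveness outcomes, state that the deciding quality-of-life contrast is the between-arm (cup vs cup+) difference in change from baseline at month 3, tested at two-sided 0.05. Estimate it as the device-by-time contrast from the mixed model already planned. That model then needs device and device-by-time terms, which the text does not now mention. Because women are individually randomised to one device for home use, a between-arm contrast also fits the design, which a paired t-test does not. Report months 1 and 2 and the trajectory as supportive estimates with 95% confidence intervals, and align the abstract and Study design wording.

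The cost is a sentence or two, with no change to data collection. With month 3 as the only deciding contrast, the simulated error is 4.7–5.3%. The downside is that a difference seen only at month 1 or 2 cannot be claimed as confirmed. The alpha and visit behind the stated 59 are unchanged, but 59 is a paired figure, and whether it suits a between-arm contrast is a separate question. The Study status section reports 16 women completed, so the wording should be settled before quality-of-life results are compared by device.

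### The cup versus cup+ quality-of-life test uses raw change from baseline without adjusting for the 0h score, an avoidable loss of efficiency (not a bias) whose power cost depends on the true effect

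*Protocol article*

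**What the plan says.** Under Data analysis, Quality of life, the device comparison is fixed in one clause: it "will be assessed by comparing the respective quality of life change using paired t-test". The same section says the team will "separately model the trajectory of quality of life across our five assessment points using mixed-effects linear regression analysis", but does not present that model as the cup versus cup+ contrast or as adjusted for baseline.

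Table 2 schedules "Quality of life (Post-fistula repair reintegration instrument" (the instrument's entry in the table) at 0h and at 1, 2 and 3 months, so every woman should have a baseline score. Community-based procedures randomises each woman individually to take home one device.

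On sizing, the target is "a mean 40% quality of life difference at three months between the cup and cup+ (measure range 0-100"). The calculation is described as "Using dependent t-test with 2-tailed, alpha error = 0.05" and "power 0.85 to avoid type 1 error, required sample size is 59". ANCOVA is mentioned only in the sample size for observed leakage.

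**The concern.** Quality of life is one of the two outcomes on which the trial is sized. A change score fixes the coefficient on baseline at 1, whatever the true relation between baseline and follow-up. When that relation is weak, subtracting baseline adds its noise to the outcome and removes little. The figures the article cites point to a weak relation.

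This is separate from the pairing problem in the same clause. Because each woman takes home only one device, cup and cup+ changes are not paired and the named test cannot be run as written. The obvious repair, a two-sample t-test on change, would leave the efficiency loss in place. At stake are the width of the interval for the device difference and, for moderate effects, the chance of detecting it.

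**Working it through.** **Inputs from the article (Sample size, Quality of life).** Baseline: "Participants reported a mean of 36.7 (SD = 19.0) at the time of fistula repair". Follow-up: mean 78.0, SD 22.7. Change: "reflecting a mean change of 40.5 (SD 28.1"). Up to 100 women are recruited, with retention above 80% expected.

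**Assumptions.** 1:1 home allocation (not stated) and 80% retention, giving 40 per arm; two-sided alpha 0.05; a two-sample test in place of the paired one.

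**1. Reproduce n = 59.** For a paired t-test (noncentral t) with power 0.85:
- Reading 40% as 0.4 SD of change: n = 58 gives 0.850, just under target, and n = 59 gives 0.856. The stated figure is reproduced, and the effect is 0.4 × 28.1 = 11.24 points.
- Reading 40% as 40 points on SD 28.1: 7 pairs would suffice. This does not reproduce 59.

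**2. Implied correlation.** r = (s0² + s1² − sc²)/(2·s0·s1) = (361 + 515.29 − 789.61)/862.6 = 0.10. Rounding of the three SDs allows 0.093 to 0.108.

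**3. Noise under each analysis.**
- Change score: SD 28.1.
- Follow-up score alone: SD 22.7.
- Baseline-adjusted: s1·√(1 − r²) = 22.7 × √(1 − 0.0101) = 22.6.
- Variance ratio, adjusted to change: 0.646, a 35% reduction.
- The change score is noisier than the follow-up score alone whenever r < s0/(2·s1) = 19.0/45.4 = 0.42.
- In general, change variance minus adjusted variance equals (s0 − r·s1)², which is never negative. Apart from one degree of freedom, adjustment cannot do worse.

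**4. Precision at 40 per arm.** Half-width = t × SD × √(2/40), with t about 1.99: 1.99 × 28.1 × 0.2236 = 12.5 points for change; 1.99 × 22.6 × 0.2236 = 10.1 points adjusted.

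**5. Power (two-sample noncentral t).**

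| Difference | Per arm | Change | Adjusted | Gain |
|---|---|---|---|---|
| 11.24 | 29.5 | 0.327 | 0.468 | 0.141 |
| 11.24 | 40 | 0.424 | 0.594 | 0.171 |
| 11.24 | 50 | 0.508 | 0.693 | 0.185 |
| 15 | 40 | 0.655 | 0.835 | 0.180 |
| 20 | 40 | 0.882 | 0.974 | 0.093 |
| 40 | 40 | >0.999 | >0.999 | 0 |

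The largest possible gain at this SD ratio is about 18.7 points.

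**6. Sensitivity to r (11.24 points, 40 per arm).** The change SD is recomputed from 19.0 and 22.7 for each r.

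| r | Change | Adjusted | Gain |
|---|---|---|---|
| 0.3 | 0.515 | 0.630 | about 11 points |
| 0.5 | 0.653 | 0.714 | about 6 points |
| 0.7 | 0.853 | 0.865 | about 1 point |

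**The case against.** Four points can fairly be made in the plan's defence.

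- **The size is conditional.** A reader might infer that the change score simply costs 17 points of power. The documents do not support that flat statement. The sizing text refers to a 0–100 measure, and the cited cohort shows changes of 54.2 in dry and 13.1 in still-leaking women, a gap of 41.1 points. If 40% means 40 points, no power is lost. The 0.4-SD reading is supported only because it alone gives 59. This objection stands.
- **The correlation is borrowed.** It is back-calculated from a surgical cohort at 6 months, not from device users at 1 to 3 months. That cohort mixes dry and leaking women: the means imply a two-thirds to one-third split, since (40.5 − 13.1)/41.1 = 0.667, and the pooled within-group change SD is then √(0.667 × 14.5² + 0.333 × 28.9²) = 20.5, well below 28.1. Also, 78.0 − 36.7 = 41.3 while the reported mean change is 40.5, so the SDs may come from slightly different sets of women. This stands for the size of the gain, not its direction (step 3 of the working).
- **It is not an error of validity.** A reader might infer bias from baseline imbalance. Under individual randomisation a between-arm comparison of change is unbiased, and chance imbalance is already reflected in its standard error. This stands.
- **The mixed model may cover it, and covariates can be left to an analysis plan.** This stands only in part. The article names the change-score test as the device comparison and describes the mixed model separately, so this is a stated choice rather than an omitted detail.

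**Conclusion.** The point holds as a recommendation on efficiency. The named comparison uses unadjusted change, and on the article's own SDs that carries about 55% more variance than a baseline-adjusted analysis (1/0.646 = 1.55). Across the effects that the wording of the target allows, the power cost runs from none at 40 points, where the gain is precision only, through about 9 points at a 20-point difference, to about 17 points at 11.2 points. These figures rest on a two-sample test, 1:1 allocation, 80% retention and r = 0.10; with a higher correlation the gain shrinks.

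It would also be wrong to infer that adjustment rescues the sample size. At 0.4 SD and 40 per arm the adjusted analysis reaches only 0.59 against the stated 0.85. A two-sample test on change would need about 113 per arm for 0.85, and an adjusted one about 113 × 0.646 = 73.

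**What to change.** Replace the paired t-test on change with a between-arm contrast of the individually randomised home arms. Use the 3-month score as outcome, or the 1–3 month scores in the mixed model already planned, with the 0h score as a covariate. Report the adjusted mean difference between cup and cup+ with its 95% CI.

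The clause has to be rewritten anyway because the pairing does not exist in the home phase, so both matters can be settled in one edit. The cost is analysis wording and one degree of freedom; the baseline score is already scheduled for every woman. State whether 40% means scale points or a standardised effect, and recompute the sample size for parallel arms on that basis, because baseline adjustment alone does not settle it.
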